### Participant timeline {13}

The time schedule for participants is illustrated in Fig. 2.

**Fig. 2 Fig2:**
[figure not shown]
Timeline. Timing and characteristics of questionnaire and treatment elements delivered in each group

### Sample size {14}

In GAIN 1.0, we found a mean difference in the improvement of 7.6 points between EUC + GAIN and EUC on the RPQ 3 months after end of treatment. In GAIN 2.0, we hypothesize a difference in the improvement of 7 points between groups on the RPQ. Using the data from GAIN 1.0, the statistical power of the stepped-wedged design can be estimated. With the assumptions of a population mean RPQ change of 9.3 points of EUC + GAIN compared with EUC, measurement variance of 137, a variance between clusters of 0.97, a statistical significance level of 5%, and a statistical power of 80%, we will need 180 participants, i.e. six participants in each of the six clusters for every of six intervention periods. In the first GAIN study, we recruited 55 citizens each year in the age group between 15 and 30 years. By expanding the range of age and offering the intervention in five clusters covering 17 municipalities, we expect to recruit at least 180 participants in the project period.

### Recruitment {15}

The research group, directing committee and one responsible key person from each cluster collaborate throughout the project to ensure the sustainability of recruitment and communication between clusters and their organisational levels. To facilitate progress in the study and ensure awareness of the study, information to GPs and collaborators will be continuously distributed through newsletters and internal communication platforms. If the recruitment rate declines, information towards GP’s and municipalities will be repeated and recruitment activities on social media will be increased.

## Assignment of interventions: allocation

### Sequence generation {16a}

A randomised schedule with time-points for start of intervention in each of the five clusters was computer-generated before trial start, by a statistician not involved in any other study procedures. The randomisation schedule is only accessible to the statistician.

### Concealment mechanism {16b}

All clusters begin as EUC (control) groups. The five clusters are then one by one randomised to begin EUC + GAIN every third month. The statistician stores the result of the randomisation procedure. Three months before a new cluster start as an intervention group, the statistician informs the project coordinator of the next cluster. The project coordinator subsequently informs the key persons in the cluster and the data manager of the project.

### Implementation {16c}

Participants are enrolled by the medical doctors after the clinical assessment at HNC. Within 2 weeks after the clinical assessment, the data manager registers the randomisation group of each participant and the participant subsequently receives an auto-generated e-mail with information on allocation.

## Assignment of interventions: Blinding

### Who will be blinded {17a}

The medical doctors assessing for eligibility are blinded to allocation of clusters. It is not possible to blind the therapists and the neuropsychologist performing GAIN in the municipalities. Only the project data manager has full access to the collected data and will not be involved in primary outcome analysis. The primary data analyser will be masked to whether a specific participant has received the intervention, but will not be masked during post hoc analyses.

### Procedure for unblinding if needed {17b}

Not relevant in the current trial.

## Data collection and management

### Plans for assessment and collection of outcomes {18a}

Data is primarily collected through online surveys using standardised and validated questionnaires e.g. data on the primary outcome (RPQ) which has shown good validity and reliability [29].

Additional data on labour market attachment will be extracted from the DREAM database. Participants' satisfaction with GAIN will be measured by The Experience of Service Questionnaire [30]. Furthermore, individual interviews with 10–20 participants will be performed [31]. The semi-structured interviews will focus on the participants’ experiences of the intervention, identify inconveniencies, and explore the possible active ingredients of GAIN. Finally, data from audio recordings of individual sessions and group sessions will be collected to check fidelity.

An overview of all measures and data sources is provided in additional files (see Additional file 1). All data collection and management are in compliance with Danish Data Protection Legislation and handling of data will be conducted according to general guidelines for encryption and anonymization (data handling number: 1–16-02–69-21).

### Plans to promote participant retention and complete follow-up {18b}

Responses to questionnaires will be observed closely, and reminders are managed by the project data manager and a project assistant. In case of no or incomplete response to the questionnaires, participants will be contacted twice by e-mail, and lastly by telephone to collect as a minimum RPQ data by an interview. Non-responders will be included in the analyses of registry-based outcomes (see the “Outcomes {12}” section and Additional file 1).

### Data management {19}

Study data are collected and managed using REDCap electronic data capture tools hosted by Aarhus University [32]. REDCap (Research Electronic Data Capture) is a secure, web-based software platform designed to support data capture for research studies, providing (1) an intuitive interface for validated data capture; (2) audit trails for tracking data manipulation and export procedures; (3) automated export procedures for seamless data downloads to common statistical packages; and (4) procedures for data integration and interoperability with external sources. All questionnaires are set up using REDCap validation features (e.g. range checks for data values). The project data manager administers REDCap access and check data quality within the REDCap system during the whole project.

### Confidentiality {27}

All data collection and storage are managed through surveys and registration forms in REDCap, except for interviews which are stored in a safety box. During the whole project period, the data manager regularly removes REDcap access for users who are no longer affiliated to the project and ensures that users are only granted necessary user rights (e.g. therapist will not have access to questionnaire data entered by the participants). Additionally, therapists will only be granted rights to see the participant’s personal registration number during intervention while the participants receive GAIN.

Data to be merged with register-based data will be extracted from REDCap and thereafter immediately uploaded to the research computers at Statistics Denmark using the Statistics Denmark encrypted upload function.

### Plans for collection, laboratory evaluation and storage of biological specimens for genetic or molecular analysis in this trial/future use {33}

The project does not involve biological specimens.

## Statistical methods

### Statistical methods for primary and secondary outcomes {20a}

Analyses are handled on an intention-to-treat basis. The primary outcome, RPQ, is analysed by using linear mixed-effects models with fixed effect of intervention arm and time (baseline, end of treatment, and 3 months after end of treatment) in interaction and random effects of clusters and subjects within clusters. Similarly, to evaluate clinical significance, we calculate the relative risk in each intervention arm of having an RPQ total score ≥ 20 at 3 months after end of treatment as well as the number needed to treat for prevention of one additional subject with RPQ total score ≥ 20. The secondary outcomes are analysed using linear mixed models similar to those described for the primary outcome using the secondary outcomes as dependent variables instead of RPQ. DREAM data will be analysed with time-to-event analysis and logistic regression.

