**Methods:**

The study is a stepped-wedge cluster-randomised trial with five clusters. The 8-week interdisciplinary GAIN program will be rolled out to clusters in 3-month intervals. Power calculation yield at least 180 participants to be enrolled. Primary outcome is mean change in PCS measured by the Rivermead Post-Concussion Symptoms Questionnaire from enrolment to 3 months after end of treatment. Secondary outcomes include participation in and satisfaction with everyday activities, labour market attachment and other behavioural measures. Self-reported outcomes are measured at baseline, by end of treatment and at 3, 6, and 18 months after end of treatment. Registry-based outcomes are measured up to 36 months after concussion.

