#### Secondary hypotheses

Participants allocated to EUC + GAIN report a greater increase in participation in IADL 3 months post-intervention compared to participants allocated to EUC only measured by the Utrecht Scale for Evaluation of Rehabilitation-Participation (USER-P) [21] as sum scores on the following dimensions: more time spend on, less limitations experienced in, and more satisfaction with participation in IADL.Participants allocated to EUC + GAIN have stronger labour market attachment 12 and 36 months post-concussion compared to participants allocated to EUC measured by sick leave, employment rate, and job stability.

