**Fig. 1 Fig1:**
[figure not shown]
The stepped wedge cluster randomised design. The stepped-wedge cluster randomised design with five clusters and six periods of each 3 months length. The white boxes illustrate the control condition (Enhanced Usual Care (EUC)) and the grey boxes intervention condition (EUC + Get Going After concussIoN (GAIN)). Recruitment, clinical assessment, and EUC take place 3 months period before each period illustrated in the figure. From power calculation, each box is estimated to involve a mean of 6 participants

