### Methods for additional analyses (e.g. subgroup analyses) {20b}

Both primary and secondary outcomes are analysed in crude and adjusted models including age, sex, previous mental health issues (no/yes), and recruitment (GP/hospital registry in Central Denmark Region).

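### The labour-market (DREAM) models are named without a cluster term, although the RPQ and the outcomes modelled like it have one; if run as named, their standard errors are too small for any positive intracluster correlation

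*Protocol article*

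**What the plan says.** All references are to the protocol article.

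- **Design.** The abstract states: "The study is a stepped-wedge cluster-randomised trial with five clusters". The Fig. 1 caption describes "The stepped-wedge cluster randomised design with five clusters and six periods of each 3 months length", and adds that "each box is estimated to involve a mean of 6 participants".
- **Hypothesis.** Under Secondary hypotheses, participants allocated to EUC + GAIN are expected to have "stronger labour market attachment 12 and 36 months post-concussion compared to participants allocated to EUC measured by sick leave, employment rate, and job stability". Section {12} lists the three registry measures as secondary outcomes: long-term sick leave, being employed and job stability.
- **Analysis of the RPQ and similar outcomes.** Section {20a} specifies a linear mixed model for the RPQ with random effects of clusters and of subjects within clusters. It then sends the secondary outcomes to linear mixed models of the same kind.
- **Analysis of the registry outcomes.** The last sentence of {20a} is all that the document gives: "DREAM data will be analysed with time-to-event analysis and logistic regression".
- **Covariates.** Section {20b} states: "Both primary and secondary outcomes are analysed in crude and adjusted models including age, sex, previous mental health issues (no/yes), and recruitment" (GP or hospital registry). Cluster is not listed.

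**The concern.** Allocation is by cluster, so a valid comparison has to allow for participants from the same cluster having correlated outcomes. Section {20a} does this for the RPQ and for the outcomes that share its model. The registry outcomes cannot inherit that term automatically, because they are given two other model families. In their ordinary form, logistic regression and Cox or log-rank analysis assume independent participants.

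The stepped wedge adds to this, because clusters contribute unequally to the two arms. The first cluster to switch spends 5 of its 6 periods under GAIN and the last spends 1 of 6. Without a cluster term, part of any difference in employment or sick leave between early and late clusters is counted as an effect of GAIN, and the standard error makes no allowance for it.

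At stake is one of the two secondary hypotheses. Labour-market attachment is also in the overall aim, and return to work is among the reasons given for the trial. Questionnaire non-responders stay in the registry analyses ({18b}), so these may be the trial's most complete results.

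**Working it through.** **Inputs from the document.** 5 clusters × 6 periods × 6 participants per cell = 180 (Fig. 1 caption). From {14}: measurement variance 137, between-cluster variance 0.97, significance level 5% (taken as two-sided), power 80%, 180 participants. The sample-size text also mentions six clusters, but 6 × 6 × 6 = 216; the stated 180 follows from five.

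**1. The plan's own figure.** The stepped-wedge variance formula with fixed period effects and a random cluster intercept, applied to this layout, gives a standard error of 2.497 RPQ points. For the difference in the statement "we hypothesize a difference in the improvement of 7 points between groups on the RPQ", 7/2.497 = 2.803, and Φ(2.803 − 1.960) = 80.0%. The stated size reproduces, so it already allows for clustering. The other figure in that section, a "population mean RPQ change of 9.3 points of EUC + GAIN compared with EUC", would give 96.1% power, so 7 is the operative value. The implied ICC for the RPQ is 0.97/(137 + 0.97) = 0.0070. The document gives no ICC for any registry outcome.

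**2. The comparison without a cluster term.** The clusters have 5, 4, 3, 2 and 1 periods under GAIN, so 15 cells (90 participants) fall in each arm. In the difference between arm means, each GAIN participant has weight +1/90 and each control participant −1/90.

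- Summed weight of the first cluster: (30 − 6)/90 = 4/15. Across the five clusters: 4/15, 2/15, 0, −2/15, −4/15.
- Sum of squares: (16 + 4 + 0 + 4 + 16)/225 = 0.178.
- Variance factor under independence: V = 1/90 + 1/90 = 1/45 = 0.0222.
- True over naive variance: [ICC × 0.178 + (1 − ICC) × V]/V = 1 + 7 × ICC, because 0.178/0.0222 = 8.

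This ratio exceeds 1 for any positive ICC. The actual size of a nominal 5% test is 2 × [1 − Φ(1.960/√ratio)]:

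| ICC | Variance ratio | SE ratio | Actual size |
|---|---|---|---|
| 0.007 (RPQ, from {14}) | 1.049 | 1.024 | 5.6% |
| 0.01 (assumed) | 1.07 | 1.034 | 5.8% |
| 0.02 (assumed) | 1.14 | 1.068 | 6.6% |
| 0.05 (assumed) | 1.35 | 1.162 | 9.2% |
| 0.10 (assumed) | 1.70 | 1.304 | 13.3% |

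This is a linear approximation for a binary outcome. Simulating plain logistic regression at an ICC of 0.05 and event rates of 50% to 70% gave 8% to 9%, in line with it.

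**3. Time-to-event.** A simulated log-rank test with about half of participants having an event had a size of 8.5%, 13.3% and 16.7% at assumed cluster log-hazard variances of 0.1, 0.2 and 0.3. Stratified by cluster, it stayed at about 5%. The variances are assumptions; the document offers none.

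**4. Price of a cluster term.** The information on the arm contrast is 180 × ½ × ½ = 45 without cluster. With cluster as a fixed effect it is 36 × (5 + 8 + 9 + 8 + 5)/36 = 35. At a 50% proportion the standard error goes from √(0.25/45) = 7.5 to √(0.25/35) = 8.5 percentage points.

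**The case against.** The strongest reply is that the sentence names two families of method and is silent on the rest. Either family can carry a random effect, a frailty, strata or robust standard errors. The preceding sentence in {20a} points secondary outcomes to models like the primary one, so the registry sentence may only be adapting the outcome type. This is a condensed article, and an analysis plan or the full protocol may settle the matter. Much of this stands. A reader might infer that the trial has decided to treat participants as independent, and the document does not say that.

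Three further inferences also go too far:

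- **The covariate list as proof.** Cluster is missing from {20b}, but that list also covers the RPQ, whose model does have a cluster effect. It lists adjustment variables and shows nothing about clustering.
- **Error rates up to about 21%.** Such a rate (20.6% at an ICC of 0.10) arises only if calendar period is modelled and cluster is not. The plan states no such model.
- **A demonstrated large inflation.** At the document's own ICC the excess is under one percentage point. Anything larger rests on assumed ICCs. The Discussion describes differences between clusters in usual care, not in employment or sick leave.

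What the reply does not remove is the contrast within one section: a cluster effect is fixed for one group of outcomes and not named for another, which has its own hypothesis. The Discussion's assurance that imperfect randomisation will be accounted for in the analysis concerns selection bias and gives no method.

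**Conclusion.** The point holds as a gap in specification with a known direction of error. Section {20a} names cluster effects for the RPQ and the outcomes modelled like it, and none for the labour-market outcomes. If the named methods are run in their ordinary form, standard errors are too small for any positive ICC. The size of a nominal 5% test is then about 5.6% at the RPQ's ICC of 0.007, and 9.2% to 13.3% at ICCs of 0.05 to 0.10.

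These figures assume equal cells of six, a common correlation within each cluster, no period term and a normal approximation. The upper range is conditional, because the document gives no ICC for employment or sick leave. The correction is worth making because it is cheap and protects a stated hypothesis.

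**What to change.** In {20a}, extend the registry sentence to say that the logistic models for the DREAM outcomes include cluster, for example as a five-level fixed effect, and that the time-to-event models are stratified by cluster. State that this applies to both the crude and the adjusted versions in {20b}. A fixed effect or strata are suggested because five clusters are few for estimating a random-effect variance or for relying on sandwich standard errors; another method that allows for clustering could be named if justified. If the analysis plan already covers this, a matching clause in the protocol is enough.

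The cost is one sentence and a few model terms, using cluster membership that is already recorded, plus the wider interval worked out above (standard error about 8.5 instead of 7.5 percentage points at a 50% proportion).

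Calendar period is a separate question. It concerns every model in {20a}, not only the registry ones, and should be settled there consistently. With cluster and period both in the model, the information falls to 14 and the standard error is √(0.25/14) = 13.4 points, so most of that loss of precision belongs to the period decision and not to this correction.

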### Interim analyses {21b}

The project does not involve interim analysis because the time schedule and design are fixed and end when the fifth cluster finishes GAIN at the end of the project period.

### Methods for additional analyses (e.g. subgroup analyses) {20b}

Both primary and secondary outcomes are analysed in crude and adjusted models including age, sex, previous mental health issues (no/yes), and recruitment (GP/hospital registry in Central Denmark Region).

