## Discussion

At present, a limited number of people with persistent PCS in Denmark are offered treatment and the available interventions are very heterogenic. There is an increased consensus that persistent PCS is best understood in terms of a multifactorial bio-psycho-social model [7] but standardised interdisciplinary interventions are lacking. The present study tests the effectiveness of the originally hospital-based GAIN intervention developed by Thastum et al. [15] in a municipality setting. The study involves a realistic and pragmatic setup of the intervention close to participants’ homes.

The present study has some limitations. First, blinding of the clinicians providing the intervention is not possible. This is a general and well-known problem in trials of behavioural interventions. Another challenge is to ensure fidelity to the treatment manual in a new and larger group of therapists. To ensure fidelity, an educational programme in GAIN to train new therapists was developed and piloted in a municipality outside the Central Denmark Region before the study commenced. Furthermore, two neuropsychologists with special knowledge of concussion and persistent PCS, cognitive behavioural therapy, and graded return to activities, are in charge of all group sessions and provide weekly supervision to therapists throughout the intervention period to ensure quality and fidelity. One of the neuropsychologists ([name]) was directly involved in the development of GAIN and was part of the interdisciplinary intervention team in GAIN 1.0. Another limitation is, that the five clusters (consisting of the 17 municipalities) participating in the trial have different approaches to usual care for people with persistent PCS, and some municipalities may offer more to participants allocated to EUC than others. This may reduce the estimated treatment effect of GAIN. Further selection bias may be an issue if proper randomisation of the five health clusters is not achieved. This will however be accounted for in the data analysis. Expectation bias may also affect both the intervention group and the control group in respectively positive and negative directions. The clinical assessment and advice at baseline may however partly adjust for the negative effect in the control group.

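### The primary outcome has a crude and an adjusted model with no rule for which decides, and neither contains calendar period

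*Protocol article*

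**What the plan says.** Section {20a} of the protocol article analyses the RPQ with "linear mixed-effects models with fixed effect of intervention arm and time (baseline, end of treatment, and 3 months after end of treatment) in interaction". Time here means the participant's own measurement occasion, not the calendar period of the rollout. The same model also carries "random effects of clusters and subjects within clusters". No patient characteristic other than the RPQ itself enters the model.

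Section {20b} then states: "Both primary and secondary outcomes are analysed in crude and adjusted models including age, sex, previous mental health issues (no/yes), and recruitment" route, meaning GP or hospital registry. The two kinds of model stand side by side, and neither is named as the one on which the primary hypothesis is judged.

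The Discussion concedes: "Further selection bias may be an issue if proper randomisation of the five health clusters is not achieved". It answers: "This will however be accounted for in the data analysis". It does not say by which model.

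The caption of Fig. 1 gives the design as "The stepped-wedge cluster randomised design with five clusters and six periods of each 3 months length", and "each box is estimated to involve a mean of 6 participants".

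**The concern.** Two models for one primary hypothesis, with no ranking, leave room to choose after the results are seen. If the crude model decides, the protection invoked in the Discussion, so far as it rests on the listed covariates, does not reach the primary conclusion. If either may be quoted, the 5% level is not held.

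Imbalance is a practical risk here. Only five units are randomised, and participants are recruited after the order has been generated. Under {16b}, the project coordinator and the cluster's key persons learn of a switch three months ahead, and the cluster's first GAIN participants are enrolled over that same interval. Section {15} plans further information to GPs and municipalities and more social media activity if recruitment declines, so the mix of recruitment routes may change over the trial.

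Calendar time makes this worse. The share of clusters under GAIN rises from none of five to all five across the periods, so any trend in case mix, usual care or recovery lines up with the intervention. Neither the crude nor the adjusted model, as listed, has a term for it.

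**Working it through.** **Inputs.** Five clusters, six periods and 6 participants per cluster-period (Fig. 1 caption); measurement variance 137, between-cluster variance 0.97, hypothesised difference 7 points, significance level 5%, power 80% and 180 participants (section {14}). Two-sided testing is assumed, as the article does not state it. Section {14} also mentions six clusters and a 9.3-point change. The check uses five clusters and 7 points because 5 × 6 × 6 = 180, whereas 6 × 6 × 6 = 216.

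**Step 1: the plan's own figure, with calendar-period effects.** The standard stepped-wedge variance (random cluster intercept, fixed period effects, different participants in each cell) is

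Var = I·s·(s + T·τ²) / [(I·U − W)·s + (U² + I·T·U − T·W − I·V)·τ²]

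- I = 5, T = 6, s = 137/6 = 22.83, τ² = 0.97.
- Number of intervention cells: U = 1+2+3+4+5 = 15.
- Sums of squared intervention counts, by period and by cluster: W = V = 1+4+9+16+25 = 55.
- Numerator: 5 × 22.83 × (22.83 + 5.82) = 3271.
- Denominator: (75 − 55) × 22.83 + (225 + 450 − 330 − 275) × 0.97 = 456.7 + 67.9 = 524.6.
- Var = 6.236, SE = 2.497.
- Power = Φ(7/2.497 − 1.96) = Φ(0.843) = 80.0%.

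The stated 180 participants and 80% power are reproduced.

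**Step 2: the same inputs without period effects.** The generalised least squares variance with only an intercept and the intervention term gives SE = 1.786 and power = Φ(7/1.786 − 1.96) = Φ(1.96) = 97.5%. About 90 participants would then give 80%. So with the Fig. 1 design and a 7-point difference, the sample size fits a model with period effects, and {20a} and {20b} do not list them.

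**Step 3: how far period and intervention overlap.** Number the periods 1 to 6, with 0, 1, 2, 3, 4 and 5 clusters under GAIN. The mean period of GAIN cells is (2+6+12+20+30)/15 = 70/15 = 4.67. The mean period of control cells is (5+8+9+8+5)/15 = 35/15 = 2.33. GAIN cells therefore lie on average 2.33 periods, or 7 months, later (a plain average that ignores cluster weighting).

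**Step 4: error rate if either model may count.** The documents do not give the share of RPQ variance explained by the four covariates; 5–10% is assumed. The correlation between the crude and adjusted test statistics under no effect is then about √(1 − R²): √0.95 = 0.975 and √0.90 = 0.949. The bivariate normal probability that at least one |z| exceeds 1.96 is 6.0% at 0.975 and 6.5% at 0.949.

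**Step 5: power with adjustment, keeping period effects and 180 participants.** Replacing 137 by 137 × (1 − R²) gives:

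| Assumed R² | SE | Power |
|---|---|---|
| 0 | 2.497 | 80.0% |
| 0.05 | 2.439 | 81.9% |
| 0.10 | 2.379 | 83.7% |

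Scaling the whole SE by √(1 − R²) instead gives 82.0% and 84.0%. Either way the range is about 82–84%.

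**The case against.** A reader might infer from the placement of the adjusted models under {20b} that the plan makes the crude model the main one. The documents do not support that. {20b} is a SPIRIT checklist label, and the sentence beneath it lists crude and adjusted models on equal terms. What the text shows is an unranked pair.

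A reader might also infer that the Discussion is contradicted. It is not: an adjusted analysis of the primary outcome is planned with its covariates named, the Discussion sentence is conditional, and it does not promise that the adjusted result will be decisive. It leaves open which result carries the protection.

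Much of the imbalance is already handled. Baseline RPQ is one of the repeated measurements, the effect is read from change over time, a random cluster effect is present, and every cluster contributes to both conditions. This stands, and limits the bias to factors that alter the course of symptoms and to calendar trends.

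A larger error rate, such as 7.8%, would need a correlation of 0.80 between the two tests, which means covariates explaining about 36% of the variance (1 − 0.80² = 0.36). Nothing in the documents suggests that.

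Finally, a separate analysis plan may rank the models. That is possible, and silence alone would be no finding. But this article itself sets out both models and their covariates, describes the primary model without period, and relies on the analysis for protection without saying which one.

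**Conclusion.** The point holds as a should-fix item. The primary analysis is not uniquely defined between crude and adjusted models, and neither version as written contains the calendar-period effect with which the planned sample size agrees.

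The choice between the two models matters modestly: a type I error of about 6.0–6.5% if either may count, and power of about 82–84% rather than 80% if the adjusted model is used. Both rest on the assumed 5–10% of variance explained, and the power figures also assume that period effects are included. The absence of period is the weightier part. Its bias cannot be sized from the documents, because it depends on a calendar trend they do not give. Adjusting for the four listed covariates alone would not remove it.

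**What to change.** State in {20a} that the single primary analysis of the RPQ is the mixed model adjusted for age, sex, previous mental health issues, recruitment route and calendar period (fixed effects for the six rollout periods), and that the primary hypothesis is judged on this model alone. Keep the crude model as a supportive analysis. In the Discussion, refer to this model where the analysis is said to account for selection bias.

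The cost is a sentence or two. The four covariates are already planned, period follows from the rollout dates, and under the assumptions above 180 participants remain enough.
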